### Relevant concomitant care permitted or prohibited during the trial {11d}

As the MIMICH trial is embedded within usual diabetes in pregnancy care, no concomitant care is prohibited for either arm of the study. Enrolment in observational studies is permitted, and co-enrolment in other intervention studies will be considered and discussed by the trial management team.

### Provisions for post-trial care {30}

Involvement in the MIMICH trial will cease following discharge from hospital after birth; all participants will receive standard postnatal care including management and treatment of diabetes. For eligible participants who agree to take part, additional follow-up visits will be offered as part of the MIMICH II study.

### Outcomes {12}

#### MIMICH

Outcomes will be recorded in the electronic case report form, hosted on REDCap. Outcomes will be collected from baseline to maternal discharge post-birth. Neonatal outcomes will be recorded up to 28 days after birth.

Primary outcome:

Third trimester foetal growth velocity, assessed by change in foetal growth z-score between 20 and 29 weeks’ gestation (average) and birth.

At each scan, the estimated foetal weight (EFW) in grams will be calculated using 2D biometry and fractional thigh volume (TVol) measurements using a standard formula [44] and converted to a z-score [43]. The delta change in z-score between the average z-score of scans performed between 20 and 29 weeks and the birthweight z-score will be calculated.

Secondary outcomes:

During pregnancy, secondary outcomes will be reported as per standard for pregnancy intervention trials. Secondary foetal growth and birthweight analyses will be assessed according to treatment group in line with the primary outcome analysis. Outcomes relating to blood glucose control (as an indicator of treatment effect) will similarly be compared between groups, as will blood pressure and hypertensive complications. Reporting and analysis of secondary outcomes will be described in full in the statistical analysis plan; to avoid issues of multiple testing, not all secondary outcomes will be compared between treatment groups. Secondary outcomes will be assessed using adjusted linear regression for continuous outcomes and chi-squared for categorical outcomes; *p* values > 0.01 and < 0.05 will be interpreted with caution. Where appropriate, outcomes will be presented with a treatment effect and confidence intervals; other outcomes will be presented with summary statistics only.

Prespecified secondary outcomes:

Adherence/acceptability:Number of missed doses—calculated as an average over pregnancy from the number of missed doses reported in the 7 days prior to each study visit (adjusted for number of study visits)Number of women unable to comply with allocated treatment (cross over)Undesirable effects of allocated treatment (number of women reporting undesirable effects associated with metformin and/or insulin/number of women receiving metformin or insulin treatment)Treatment satisfaction with allocated medication regime (questionnaire)Acceptability of allocated medication regime (questionnaire)

Secondary foetal growth research outcomes:Distribution of foetal growth z-scores between treatment groups and within prespecified subgroupsComparison of foetal growth z-scores (conventional Hadlock formula EFW without TVol measurement) between treatment groups and within prespecified subgroupsNumber of small and large for gestational age infants (defined using birthweight z-score) derived from the WHO birthweight centiles [43]

Standard secondary maternal outcomes:Gestational weight gain (difference between baseline and 30–34-week visit weight adjusted for number of weeks)Episodes of severe hypoglycaemia (blood glucose < 3 mmol/L)—total number reported over the treatment duration reported at each study visitMean (fasting and 1 h post meal) daily glucose and % time in target—captured from HBGM and/or CGM sensors at each study visit and summarised for each trimesterMaximum achieved dose of metformin (standard care arm only)Total insulin dose (units/kg/day) at final study visit (short- and long-acting insulin reported separately)Mean change in insulin dose (units/day) from baseline to last study visitNeed for antihypertensive therapy—study visits and pregnancy outcome case note reviewPre-eclampsia (defined according to ISSHP guidelines)—study visits and pregnancy outcome case note reviewIndicated delivery (induction of labour or pre-labour rupture of membranes (PROM) with stimulation of labour or pre-labour caesarean section)—pregnancy outcome case note reviewMode of onset of birth (spontaneous, induction of labour, PROM with stimulation of labour, pre-labour caesarean section)—pregnancy outcome case note reviewIndication for onset of birth—pregnancy outcome case note reviewMode of birth—pregnancy outcome case note reviewPostpartum haemorrhage (blood loss > 1000 mL)—pregnancy outcome case note reviewShoulder dystocia—pregnancy outcome case note reviewTotal number of postnatal hospital inpatient days—pregnancy outcome case note review

Neonatal outcomes—clinical birth outcomes obtained from case note review:Foetal loss (prior to 24 weeks’ gestation and from 24 + 0 weeks’ gestation (stillbirth))Known early neonatal death (up to 7 days from birth)Known late neonatal death (between 7 and up to 28 days from birth)Gestational age at birthBirthweight, birthweight centile, birthweight z-scoreNeonatal unit admission (separation of baby from mother), principal recorded indication for neonatal unit admission and length of stay in neonatal unit (and level of care)Apgar score (5 min)Umbilical arterial pH at birthNeed for respiratory support and type of respiratory support neededLowest blood glucose measurement and need for treatment for neonatal hypoglycaemiaNeonatal seizures, intracranial haemorrhage, necrotising enterocolitisBreastfeeding at discharge

Exploratory outcomes—additional research outcomes:Longitudinal changes in angiogenic markers (sFlt, PlGF)—measured in research blood samples (batch analysis end of study)Maternal skinfold measurements (delta change from baseline visit adjusted for gestation)HOMA-IR (measured at 30–34 weeks ± 2 weeks)—measured in research blood samples (real time in the biochemistry lab)Ponderal index (foetal weight in grams × 100/(foetal length in centimetres)Neonatal measurements within 72 h of birth (crown-heel lengths, weight, head/abdominal circumferences, biceps, triceps, subscapular skinfold thicknesses)Erythropoietin (marker of intrauterine stress) [45, 46]

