### MIMICH sequence generation {16a}

The sequence will be computer generated within the Sealed Envelope platform. Participants will be randomised (1:1) using minimisation with a random element controlling for:Type of diabetes (diagnosed < 24 weeks’ gestation, diagnosed > 24 weeks’ gestation)Risk factor for placental disease (uteroplacental or maternal risk factor)Gestational age (6 + 0 to 11 + 6 weeks, 12 + 0 to 23 + 6 weeks, 24 + 0 to 30 + 0 weeks)

The sequence will be computer generated. Participants will be randomised (1:1) using minimisation with a random element controlling for:Type of diabetes (diagnosed < 24 weeks’ gestation, diagnosed > 24 weeks’ gestation)Risk factor for placental disease (uteroplacental or maternal risk factor)Gestational age (6 + 0 to 11 + 6 weeks, 12 + 0 to 23 + 6 weeks, 24 + 0 to 30 + 0 weeks)

For each new participant, the algorithm calculates the imbalance that would result from assigning them to each treatment arm. The arm that minimises imbalance is selected with high probability (default 80%). With the remaining probability (20%), allocation is made to the alternative arm. If both arms would produce equal balance, allocation is determined with equal probability (50:50).

This approach maintains a close balance between groups across important prognostic factors, whilst the random element preserves allocation unpredictability. The randomisation sequence is generated and maintained centrally within the Sealed Envelope system, ensuring full allocation concealment from investigators and participants until the point of assignment.

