## Statistical methods

### Statistical methods for primary and secondary outcomes {20a}

The statistical analysis will be conducted according to the approved statistical analysis plan. Baseline characteristics of the trial population will be presented as mean and standard deviation (or median and interquartile range as appropriate). The main analysis will be an intention to treat analysis for the primary and secondary outcomes. For the primary outcome, the average z-score for estimated foetal weight (calculated using the modified EFW formula which incorporates TVol [44]) performed between 20 and 29 weeks will be calculated. This will be 1–3 scans per woman. The delta between the birthweight z-score and the 20–29-week z-score will be calculated. Delta z-scores will be compared between treatment groups using linear regression models adjusted for baseline z-score and minimisation variables (these will be confirmed in the final statistical analysis plan). All secondary outcomes will be reported as described in the outcomes section and analysed in accordance with the prespecified statistical analysis plan.

Missing data for baseline prognostic factors are not anticipated since they must be recorded to allocate treatment. All observed outcome data will be included in the analyses. As this is an exploratory study, we will focus on reporting the amount of missing data. We will report the number (%) of participants withdrawing fully from the trial and lost to follow-up by treatment arm. Reasons for missingness may be important, and these will be tabulated by treatment arm and documented as far as possible. Main analyses will be performed using STATA (StataCorp, College Station, TX, USA).

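### Categorical secondary outcomes are assigned an unadjusted chi-squared test although allocation is minimised and the primary analysis adjusts for the minimisation variables

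*Protocol article*

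**What the plan says.** All references are to the protocol article.

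- **Method by outcome type** (Outcomes {12}, MIMICH): "Secondary outcomes will be assessed using adjusted linear regression for continuous outcomes and chi-squared for categorical outcomes". Adjustment is attached to the continuous outcomes only.
- **Growth outcomes** (same paragraph): "Secondary foetal growth and birthweight analyses will be assessed according to treatment group in line with the primary outcome analysis". SGA and LGA counts are listed among the secondary foetal growth outcomes.
- **What is compared** (same paragraph): glucose control, blood pressure and hypertensive complications are named for comparison between groups, but "to avoid issues of multiple testing, not all secondary outcomes will be compared between treatment groups".
- **Effect estimates** (same paragraph): "Where appropriate, outcomes will be presented with a treatment effect and confidence intervals; other outcomes will be presented with summary statistics only".
- **Deferral** (same paragraph): "Reporting and analysis of secondary outcomes will be described in full in the statistical analysis plan".
- **Allocation** (MIMICH sequence generation {16a}): "Participants will be randomised (1:1) using minimisation with a random element controlling for" type of diabetes, type of placental risk factor and gestational age. The balancing arm is chosen with 80% probability. The section describes these factors as prognostically important.
- **Primary analysis** (Statistical methods {20a}): linear regression "adjusted for baseline z-score and minimisation variables".

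**The concern.** Minimisation makes the arms more alike on the chosen factors than simple randomisation would. If those factors predict the outcome, the difference between arms varies less from trial to trial than an unadjusted test assumes. The unadjusted test then uses too large a variance: its true type I error is below nominal and some power is lost. A model that contains the factors restores the nominal level. The article follows this logic for the primary outcome but names a test without covariates for the categorical secondary outcomes.

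These outcomes matter because SGA, LGA and pre-eclampsia help to show whether a shift in the growth z-score is a benefit or a harm. The article also asks for caution with p-values between 0.01 and 0.05, so behaviour at the 0.01 level counts too.

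The article is inconsistent for SGA and LGA. As growth outcomes defined from the birthweight z-score they should follow the adjusted primary analysis; as categorical outcomes they fall under chi-squared.

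**Working it through.** **1. The plan's own figure.** Sample size considerations {14} give 190 women (95 per group) for a difference of 0.41, SD 1.0 and 80% power. With two-sided alpha 0.05 (assumed), n per arm = 2(1.96 + 0.84)²/0.41² = 93.4, so 94 per arm or 188 in total; power at 95 per arm is 80.7%. The figure reproduces, so N = 190 is used below. The article gives no figure for the categorical analyses.

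**2. Simulation set-up.**
- From the article: N = 190; 1:1 minimisation on the three factors; 80% to the balancing arm, 50:50 on ties; an event rate of about 20%, the rate it expects for SGA.
- Assumed, because the article gives nothing: half the women in each diabetes category; 40% with one risk-factor type; later-diagnosed women all in the last gestation band and the others spread evenly over the three bands. The odds ratio (OR) for risk-factor type is varied, diabetes type has 0.7 of that effect on the log scale, and gestation has no effect of its own.
- Analyses: Pearson chi-squared, and logistic regression (Wald test) on arm plus the minimisation factors. There were 5,000 null trials per row, so the Monte Carlo standard error at 5% is √(0.05 × 0.95/5000) = 0.3 points.

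**3. Type I error.**

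| Assumed OR | Chi-squared, nominal 5% | Adjusted, nominal 5% | Chi-squared, nominal 1% | Adjusted, nominal 1% |
|---|---|---|---|---|
| 1 | 4.8% | 5.0% | 1.0% | 0.8% |
| 2 | 4.7% | 5.2% | 0.9% | 1.0% |
| 3 | 4.3% | 5.1% | 0.6% | 0.8% |
| 5 | 3.6% | 4.9% | 0.5% | 0.8% |
| 9 | 2.7% | 4.9% | 0.3% | 0.7% |

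The OR 2 row cannot be told from 5% within simulation error. At the 1% level the adjusted Wald test is itself slightly conservative, so not all of the shortfall there comes from omitting the factors.

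**4. Power at the 5% level**, for an assumed treatment OR of 0.4 (3,000 trials per row), chi-squared against adjusted: 56.0% and 56.2% (OR 2), 54.2% and 55.9% (OR 3), 51.1% and 55.8% (OR 5). The losses are 0.2, 1.7 and 4.7 points.

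**5. Cross-check by formula.** With complete balance, the type I error of the unadjusted test is 2(1 − Φ(1.96/√(1 − R²))), where R² is the share of outcome variance explained by the factors. At OR 5 the four risk-by-diabetes cells have event probabilities 0.059, 0.160, 0.235 and 0.485, with weights 0.3, 0.3, 0.2 and 0.2. The mean is 0.210, the variance between cells 0.0229, and R² = 0.0229/(0.210 × 0.790) = 0.138. Then 1.96/√0.862 = 2.11, which gives 3.5% against 3.6% simulated. By the same steps OR 3 gives R² = 0.070 and 4.2% against 4.3%. Formula and simulation agree.

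**6. Event rate.** The article expects pre-eclampsia in 12–18%, below the rate simulated. Resetting the intercept so that the mean is 15% at OR 5 gives R² = 0.11 and, by the formula, 3.8%. The effect for pre-eclampsia would be slightly smaller than the table shows.

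**The case against.** The strongest reply is that the article leaves secondary analyses to a statistical analysis plan that is not shown, and that effect measures and rules for sparse data belong there. That stands for missing detail, and none is alleged here. It does not cover a method that the article does name: a plan that follows the sentence inherits the unadjusted test, and one that departs from it contradicts the published protocol.

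The second reply is that the effect is small, errs towards caution, and depends on factor strengths that the article does not give. This also stands and limits the weight of the point.

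A reader might infer more than the article supports:

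- **That no effect estimates will be given.** The next sentence promises a treatment effect and confidence interval where appropriate. What it leaves open is which categorical outcomes receive one and from which model.
- **That rare neonatal events will be tested by chi-squared.** Neonatal unit admission, deaths, seizures and necrotising enterocolitis are not named as compared, and the article allows summary statistics only.
- **That SGA and LGA are plainly unadjusted.** The text is contradictory for them.
- **That the 5% test runs at 3.9% or 2.8%.** By the formula above these need R² of 0.10 or 0.20. In the simulated settings that means an OR between 3 and 5, or approaching 9, and the article supports neither.
- **That wide intervals show the flaw.** With 20% events and 95 per arm the half-width for a risk difference is 1.96√(2 × 0.2 × 0.8/95) = 0.114. That comes from sample size, and adjustment would change it little.

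**Conclusion.** The point holds as a modest fault in a stated secondary analysis. The unadjusted test is at odds with the minimised design and with the adjusted primary model. It clearly applies to pre-eclampsia and other hypertensive complications, and it produces a contradiction for SGA and LGA.

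The size is negligible to small if the minimisation factors are weakly or moderately prognostic (type I error 4.3–4.7%, power loss up to about 2 points at OR 2–3). It becomes material only if they are strong (3.6% and about 5 points at OR 5). These figures rest on assumed factor strengths and category sizes, on N = 190 and on about 20% events. The error does not create false positives and leaves the primary result untouched. The statistical analysis plan may already settle the matter.

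**What to change.** 1. For the categorical outcomes that are formally compared, replace chi-squared with a binary regression on arm plus the minimisation factors: for example logistic regression with standardisation, or Poisson regression with robust standard errors.
2. Take the treatment effect and 95% confidence interval that the article already promises from that model, as a risk difference or risk ratio, and name the measure.
3. Reconcile the two statements for SGA and LGA so that one adjusted method applies, and say whether the baseline z-score is included as in the primary model.
4. Keep sparse outcomes descriptive, as the article already allows.

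The cost is revised wording and a little more analysis code. The minimisation factors are recorded at randomisation, so no extra data or participants are needed.

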### Eligibility criteria {10}

#### Inclusion criteria

Singleton pregnancy between 6^+0^ and 30^+0^ weeks’ gestation inclusiveAged 18 years or over and willing and able to give informed consentDiagnosis of diabetes in pregnancyType 2 diabetes diagnosed before pregnancy ORType 2/GDM diagnosed < 24 weeks’ gestation: abnormal glucose tolerance test^a^, abnormal HBGM^b^ and/or HbA1C ≥ 41 mmol/L ORGDM (diagnosed 24–30 weeks): HbA1C ≥ 41 mmol/L and/or abnormal glucose tolerance test^a^Abnormal HBGM.^b^ (≤ 30 weeks)Presence of at least one risk factor for placental diseaseBP ≥ 130 and/or ≥ 80 mmHg (clinic blood pressure)Pulse wave velocity ≥ 9 m/sAge ≥ 35 yearsNulliparousPre-eclampsia and/or small for gestational age (< 10th centile) in a prior pregnancyCurrent SGA (EFW < 10.th centile)Mean uterine artery PI ≥ 95th centile^c^Placental growth factor < 10th centile^c^EFW ≤ 50th centile (if ≥ 22 weeks)^c,d^

^a^Abnormal glucose tolerance test: fasting glucose ≥ 5.3 mmol/L and/or 2 h ≥ 8.5 mmol/L.

^b^Abnormal home blood glucose monitoring (HBGM): 3 abnormal readings (fasting blood glucose ≥ 5.3 mmol/L, 1 h post meal ≥ 7.8 mmol) in 1 week.

^c^To be confirmed/measured at the baseline visit.

^d^WHO population centiles [43].

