**Fig. 1 Fig1:**
[figure not shown]
Timeline of protocol for MIMICH participants

**Table 1 Tab1:** Schedule of visits and trial procedures for MIMICH

Procedures	Participant identification antenatal clinics	Baseline visit	Intervention period (study visits every 4 ± 2 weeks)	Fasting visit (30–34 weeks ± 2 weeks)	At/after birth
Routine antenatal visit	x	x	x	x	
Eligibility check	x	x			
Written informed consent		x			
Randomisation		x			
Collection of baseline characteristics (demographics, obstetric and medical history, medication)		x			
Confirmation of willingness to continue intervention			x	x	
Study visits every 4 ± 2 weeks (including ultrasound scan, BP, weight)		x	x	x	
Skinfold measurements		x		x	
Adherence with treatment: dose of insulin/metformin and self-reported number of missed doses in previous 7 days		x	x	x	x
Summary of glycaemic control and number episodes of hypoglycaemia (preceding 7 days)		x	x	x	x
Fasting blood samples (30–34 weeks only)				x	
Acceptability questionnaire completion [hard copy]				x	
Review of pregnancy complications/events			x	x	x
Research blood samples		x	x	x	x
Safety reporting			x	x	x
Pregnancy outcome/case note review					x
Collection of placenta and cord blood					x
Measurement of infant (within 5 days of birth)					x

Figure 2 and Table 2 depict the timelines for postnatal follow-up. As MIMICH II is concerned with postnatal care, all study visits will fall outside of routine care.

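### Severe hypoglycaemia is defined as a total over treatment but captured only in 7-day windows before visits, with no adjustment for the number of windows observed

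*Protocol article*

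**What the plan says.** Four parts of the protocol bear on this outcome.

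- **Definition.** Outcomes {12}, standard secondary maternal outcomes, lists episodes of severe hypoglycaemia (below 3 mmol/L) as a total across treatment, as reported at study visits. No denominator is given.
- **Capture.** Table 1 (Participant timeline {13}) has the row "Summary of glycaemic control and number episodes of hypoglycaemia (preceding 7 days"). It is marked at baseline, in the intervention period, at the fasting visit and at or after birth. The visit row reads "Study visits every 4 ± 2 weeks (including ultrasound scan, BP, weight").
- **A comparable outcome.** Missed doses, under adherence in Outcomes {12}, are averaged from those "reported in the 7 days prior to each study visit (adjusted for number of study visits").
- **Analysis.** Outcomes {12} states "Secondary outcomes will be assessed using adjusted linear regression for continuous outcomes", with chi-squared for categorical ones. It says that blood glucose control outcomes are compared between groups, that not every secondary outcome will be compared, and that the statistical analysis plan will give the full detail.

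**The concern.** The definition and the capture schedule describe different quantities. A total across treatment needs all treatment time to be observed, whereas Table 1 observes one week per visit. The recorded total therefore depends on how often a woman is seen and for how long, as well as on her episode rate. The authors dealt with this for missed doses but not here.

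The baseline mark adds an ambiguity. Under Implementation {16c}, randomisation follows completion of all baseline measurements, so the week reported at baseline precedes allocated treatment. Nothing says that it is left out of the total.

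The outcome matters because the intervention arm manages glucose with diet and insulin alone, and hypoglycaemia that does not need hospitalisation is on the list of events not reported as adverse events (Adverse event reporting {22}, maternal events). For those episodes, this secondary outcome is the listed between-arm measure.

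**Working it through.** **The plan's own figures.** The protocol gives no hypoglycaemia rate, visit count or power for this outcome, so there is nothing specific to reproduce. The illustration below borrows only the 95 per arm from Sample size {14}. That figure reproduces, assuming two-sided 5%: n = 2 × (1.96 + 0.84)² × 1.0² / 0.41² ≈ 93.4, so 94 per arm; with 95 per arm, power is 80.7%.

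**Step 1: share of treatment time observed.** With one 7-day window per visit, spacing of s weeks observes about 1/s of the time: 1/2 at 2 weeks, 1/4 at 4 weeks, 1/6 at 6 weeks.

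**Step 2: windows per woman.** Inputs: entry "Singleton pregnancy between 6^+0^ and 30^+0^ weeks" (Inclusion criteria); spacing of 2 to 6 weeks (Table 1); follow-up to 38 weeks (assumed). Visits = 1 + floor((38 − entry) / spacing).

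| Entry | Spacing | Windows | Share of weeks |
|---|---|---|---|
| 12 weeks | 2 weeks | 1 + 13 = 14 | 14/26 = 54% |
| 12 weeks | 4 weeks | 1 + 6 = 7 | 7/26 = 27% |
| 12 weeks | 6 weeks | 1 + 4 = 5 | 5/26 = 19% |
| 6 weeks | 4 weeks | 1 + 8 = 9 | 9/32 = 28% |
| 30 weeks | 4 weeks | 1 + 2 = 3 | 3/8 = 38% |

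These counts include the baseline visit and omit the record at or after birth. Swapping one for the other changes a count by at most one. For a 12-week entrant, the same true rate gives a 14/5 = 2.8-fold range in the raw total across the permitted spacings.

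**Step 3: effect on the arm comparison.** A simulation of 3000 trials per setting used 95 women per arm and no true difference in rate. Its assumptions, none from the documents, were: entry uniform over 8 to 30 weeks, follow-up to 38 weeks, spacing varying by half a week either way around the arm's mean, gamma-Poisson counts with dispersion 1, and 0.1 to 1.0 episodes per window. Both the raw total and the total per visit were analysed by linear regression adjusted for entry gestation. Rejection rates at nominal 5%:

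| Spacing, arm A v arm B | Mean visits | Raw total | Per visit |
|---|---|---|---|
| 4 v 4 weeks | 5.3 v 5.3 | 4.8–5.2% | 4.9–5.1% |
| 4 v 3.5 weeks | 5.3 v 6.0 | 6.8–11.1% | 4.6–5.0% |
| 4 v 3 weeks | 5.3 v 6.9 | 18.9–35.1% | 4.4–4.8% |
| 4 v 2.5 weeks (extreme) | 5.3 v 8.2 | 46–76% | 4.5–5.0% |

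The 4 v 3 row agrees with direct arithmetic. The gap in visits is 6.88 − 5.28 = 1.60, so at 0.3 episodes per window the spurious excess is 1.60 × 0.3 = 0.48 episodes per woman, which the simulation returned. Over 0.1 to 1.0 episodes per window the excess was 0.16 to 1.58.

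**Step 4: where an arm difference could arise.** Care is open label (Blinding {17a and 17b}), and trial visits run alongside routine ones, so spacing may follow clinical need. For women who discontinue, antenatal data collection ends (Plans to promote participant retention {18b}). Indicated delivery and gestational age at birth are themselves outcomes, so treatment could shorten observation. Minimisation uses entry gestation, beginning "Gestational age (6 + 0 to 11 + 6 weeks"; this balances potential follow-up at entry but not what happens after randomisation.

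**The case against.** Several points on the other side are sound.

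- **The model is not fixed here.** A reader might infer that the protocol puts this count into linear regression. It does not. That method is named for continuous outcomes, episode counts are not mentioned, and the analysis is left to a statistical analysis plan that is not at hand. This stands. What the protocol itself fixes is the definition and the capture window.
- **Linear regression is not the fault.** On a per-visit rate it rejected 4.4–5.1% of the time in every setting. The missing denominator causes the error, so a count model is a preference and not a necessity.
- **Bias needs an arm difference in observed windows.** Both arms share one schedule, and entry gestation is a minimisation factor. With equal spacing the raw total rejected about 5%. This stands: the protocol does not say that visit frequency will differ by arm.
- **The definition can be read as the sum of visit reports.** On that reading it does not contradict Table 1 outright. The sum still has no denominator, and calling it a total across treatment still overstates what was observed.
- **Adverse event reporting is a second source.** Hypoglycaemia requiring hospitalisation falls outside the list of unreported events, and adverse events are collected from consent to discharge. This narrows the gap to episodes that do not need hospitalisation.

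Two further inferences lack support. The documents give no episode rate, so nothing shows that most women will have zero episodes. Nothing in them supports extending the point to neonatal length of stay.

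**Conclusion.** The point holds as a mismatch between definition and capture, with a missing denominator. At 4-weekly visits the recorded total covers about a quarter of treatment time. It scales with visits, up to 2.8-fold for a 12-week entrant followed to 38 weeks, and could include a week before randomisation.

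With equal visit frequency the arm comparison is not biased; the total understates the burden and carries extra noise. It becomes biased if observed windows differ by arm. The 19–35% false-positive range for 4- v 3-weekly visits illustrates that under assumed spacing, rates and dispersion, and is not a forecast for this trial. Even an assumed half-week difference gave 7–11%. Outcomes that are only summarised are affected too, since a raw total without observed time misleads in a table. The primary outcome is untouched.

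**What to change.** Reconcile the outcome list with Table 1. Define the outcome as severe hypoglycaemia episodes per observed 7-day window after randomisation, and state that the baseline window is excluded from it. If arms are compared, compare that rate, adjusted for the minimisation factors: either linear regression on the per-window rate or a count model with log windows as offset would serve. Report the number of windows by arm whether or not a test is done.

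The cost is a change of wording and a few lines of code, since the number of visits is already recorded. The effect becomes a rate difference or rate ratio and no longer a total. One limit remains: a per-window rate assumes that the weeks before visits are typical of treatment. If visits are brought forward because of hypoglycaemia, the rate is affected too, which is a further reason to show windows by arm.
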